# The combined effect of Parathyroid hormone (1-34) and whole-body Vibration exercise in the treatment of OSteoporosis (PaVOS)- study protocol for a randomized controlled trial

**DOI:** 10.1186/s13063-018-2551-5

**Published:** 2018-03-16

**Keywords:** Osteoporosis, Whole-body vibration, Parathyroid hormone, Teriparatide, Bone mineral density, Bone quality, RCT

## Abstract

**Background:**

PaVOS is a randomized controlled trial (RCT) which aims to address the use of whole-body vibration exercise (WBV) in combination with parathyroid hormone 1-34 fragment teriparatide (PTH 1-34) treatment in patients with osteoporosis. PTH 1-34 is an effective but expensive anabolic treatment for osteoporosis. WBV has been found to stimulate muscle and bone growth. Animal studies have shown a beneficial effect on bone when combining PTH 1-34 with mechanical loading. A combined treatment with PTH 1-34 and WBV may potentially have beneficial effects on bone and muscles, and reduce fracture risk.

**Methods/design:**

PaVOS is a multicenter, assessor-blinded, superiority, two-armed randomized controlled trial (RCT).

Postmenopausal women (*n* = 40, aged 50 years and older) starting taking PTH 1-34 from outpatient clinics will be randomized and assigned to a PTH 1-34 + WBV-exercise group (intervention group), or a PTH 1-34-alone group (control group).

The intervention group will undergo WBV three sessions a week (12 min each, including 1:1 ratio of exercise: rest, 30 Hz, 1 mm amplitude) for a 12-month intervention period. Both the intervention and the control group will receive PTH 1-34 treatment (20 μg s.c. daily) for 24 months. After 12 months the WBV group will be re-randomized to stop or continue WBV for an additional 12 months.

The primary endpoint, bone mineral density (BMD), will be measured by dual-energy x-ray absorptiometry of the total hip and the lumbar spine.

Secondary endpoints, bone microarchitecture and estimated bone strength, will be assessed using high-resolution peripheral quantitative computed tomography (HR-pQCT) of the radius and tibia. Serum bone turnover markers (carboxy-terminal collagen crosslinks (CTX), amino-terminal propeptide of type-I collagen (P1NP), and sclerostin) and functional biomarkers (Timed Up and Go (TUG), Short Physical Performance Battery (SPPB), grip strength, and leg extension power) will be measured to assess the effect on bone turnover, muscle strength, balance, and functionality. Quality of life (EQ-5D), physical activity (IPAQ) and fear of falling (FES-I) will be assessed by questionnaires. Data on adherence and falls incidence will be collected.

**Discussion:**

The PaVOS study will investigate the effects of WBV in combination with PTH 1-34 on bone parameters in postmenopausal women.

**Trial registration:**

ClinicalTrials.gov, ID: NCT02563353. Registered on 30 September 2015.

**Electronic supplementary material:**

The online version of this article (10.1186/s13063-018-2551-5) contains supplementary material, which is available to authorized users.

## Background

### Introduction

Osteoporosis is defined by the World Health Organization (WHO) as a disease with low bone mass and impaired microarchitecture leading to a high risk of fragility fractures [1].

Fragility fractures of the hip are associated with significant morbidity, institutionalization, and a 1-year mortality of > 20% [2]. Vertebral fractures are also associated with osteoporosis and can lead to significant pain, disability, morbidity, and reduced quality of life [3]. Osteoporotic fractures cause a significant disease burden in developed countries [4] and a recent study of the societal burden imposed by osteoporotic fractures in Denmark showed an estimated yearly cost of €1.563 billion [5].

The parathyroid hormone 1-34 fragment teriparatide (PTH 1-34) is the most commonly used anabolic agent for the treatment of osteoporosis. The Fracture Prevention Trial showed that PTH 1-34 significantly reduced the incidences of vertebral and non-vertebral fractures [6]. However, the relatively high cost of PTH 1-34 (€7103 per year) restricts its use in osteoporotic patients to those with the highest fracture risk or, those who had inadequate response to, or cannot tolerate more commonly used anti-osteoporotic agents, such as bisphosphonates [7]. Thus, any intervention that can boost the efficacy of PTH 1-34 could make it more cost-effective. Furthermore, as the length of PTH 1-34 treatment is limited (licensed for up to 18–24 months only), and maximizing its response by such augmentation would be desirable, in terms of reducing fracture risk in individual patients and by potential cost-saving implications.

Mechanical loading is also known to increase bone formation and load-bearing exercise is an important component in maintaining and improving bone health. Studies have shown that load-bearing exercise can increase bone mineral density (BMD) [8].

A synergistic or additive effect of combined PTH 1-34 treatment and mechanical loading has been reported [9, 10]. Not all older people, however, can undertake high-intensity or weight-bearing exercise. A proposed alternative is whole-body vibration (WBV) therapy which, like weight-bearing exercise, stimulates muscles and bones. In some studies, WBV increases the anabolic (bone-building) effects in bone tissue, as well as increasing BMD [11, 12]. One hypothesis suggests that the effects of vibration directly activate mechanosensors in bone cells [13]. Like weight-bearing exercise [14], WBV may thus improve muscle strength and power by increasing neuromuscular activation [15]. In healthy volunteers, the effects of vibration therapy on muscle strength and performance were similar to those of short-term resistance exercise [14].

WBV therapy may also improve blood circulation in muscle and bone and increase the supply of nutrients needed to build bones [16]. Platforms for WBV are now commercially available and are used in gyms, as an alternative form of exercise. Animal studies with the combination of PTH analogs and WBV are few and with diverse results. One study with low-magnitude vibration and PTH 1-34 in mice showed no synergy in increasing bone mineral content after 8 weeks of treatment [17]. A recently published study showed that the combination of noise-like WBV and PTH treatment of fracture healing produced an additive effect in increasing bone formation and enhancing the mechanical function of the bone [18]. Human studies have shown that vibration can be anabolic to bone [12, 19, 20], and a study performed by one of our group (TM) has shown that WBV is well tolerated even by frail, older individuals and increases muscle strength and bone-formation markers [19]. Adding mechanical loading in the form of WBV to the treatment with an anabolic agent may improve treatment outcomes further increasing BMD and reducing the risk of fracture.

#### Study objectives

To determine if WBV in addition to standard PTH 1-34 treatment has a greater effect in osteoporotic patients compared to standard PTH 1-34 treatment alone on:BMDBone microarchitectureMarkers of bone formation and resorptionMuscle function and balanceTo assess the safety and adherence to WBV in osteoporotic patients

## Methods/design

### General design

This will be a multicenter, assessor-blinded, superiority, two-armed RCT in osteoporotic patients starting standard PTH 1-34 treatment. In Denmark, PTH 1-34 is used for the treatment of severe osteoporosis, and the cost is reimbursed if patients have a lumbar spine or total hip T-score ≤ − 3 combined with at least one clinical vertebral fracture (compression ≥ 25%) within the past 3 years or at least two vertebral fractures (compression ≥ 25%) independently of BMD. Participants will be randomized to PTH 1-34 treatment alone or to combined PTH 1-34 treatment and WBV (see Fig. 1). The study will be reported according to the Consolidated Standards of Reporting Trials (CONSORT) extension to non-pharmaceutical interventions and the Standard Protocol Items: Recommendations for Interventional Trials (SPIRIT) 2013 Checklist for RCTs (Additional file 1).

**Fig. 1 Fig1:**
[figure not shown]
The Standard Protocol Items: Recommendations for Interventional Trials (SPIRIT) Figure with the schedule of enrollment, interventions, and assessments. *BMD* bone mineral density; *Bone turnover biomarkers* procollagen type-1 amino-terminal propeptide, carboxy-terminal type-1 collagen crosslinks, sclerostin; *HR-pQCT* high-resolution peripheral quantitative computed tomography; *FES-I* Falls Efficacy Scale International; *Functional biomarkers*: Short Physical Performance Battery, Timed Up and Go, grip strength, leg extension power; *IPAQ* International Physical Activity Questionnaire.

### Participants

Postmenopausal women over the age of 50 years attending either of the following outpatient clinics will be recruited: the Osteoporosis Clinics at Odense University Hospital (Svendborg or Odense), the Department of Geriatrics at Odense University Hospital, the Department of Endocrinology at Hospital of Southwest Denmark, the Department of Endocrinology at Hospital Lillebaelt or the Department of Endocrinology and Internal Medicine, Aarhus University Hospital.

#### Inclusion criteria

Postmenopausal women aged ≥ 50 years starting PTH 1-34 treatment for osteoporosis

#### Exclusion criteria

Currently taking oral glucocorticoidsUnable to give informed consentUnable to stand for 1 min at a time on the vibration platformContraindications to WBV (e.g., joint prosthesis, pacemakers)

### Intervention

After instructions by nurses in the treating clinics all participants will self-administer subcutaneously (s.c) PTH 1-34 (20 μg s.c. daily) during the study. The participants follow each clinic’s control program including measurements of serum calcium and creatinine throughout the study. Medical records will be used to check the adherence to the PTH 1-34 treatment.

Half of the participants will be randomized to an intervention group, receiving WBW as add-on treatment. WBV will be undertaken using power plate My5 (Power plate®, UK). The power plate machine oscillates in all three planes, with a frequency of 30 Hz and amplitude of 1 mm (low displacement) and peak acceleration of 35.53 ms^-2^ rms (3.6 *g*).

The WBV intervention will be performed three times a week according to a training protocol (Table 1). The vibration platforms will be delivered and installed in the participant’s own home and instructions for use and the training program will be given by one of the investigators (DJ).

**Table 1 Tab1:** Training protocol

Week	First training day	Second training day	Third training day
1	30 s × 2	30 s × 3	30 s × 4
2	1 min × 1	1 min ×2	1 min × 3
3–5	1 min × 4	1 min × 4	1 min × 4
6–7	1 min × 5	1 min × 5	1 min × 5
8 to the end of study	1 min × 6	1 min × 6	1 min × 6

*Min* minutes, *s* seconds

The WBV intervention will be conducted with the knees slightly bent (at approximately 20°) to prevent vibrations to cause side effect as dizziness from the vibration transmitted to the head. The training period will be followed by a resting period in the ratio 1:1 and the training days will be conducted with a resting day in between.

### Randomization

After informed consent and collection of baseline data, participants will be randomized into two groups: PTH 1-34 treatment alone or PTH 1-34 treatment + WBV (Fig. 2). The randomization is a web-based, computer-generated block randomization with no stratification. Block size is created by a data manager and the size is unknown to the investigators until the end of the study. Allocation will be concealed to the participants and the investigators until after collection of baseline data.

**Fig. 2 Fig2:**
[figure not shown]
Timeline for participants. Figure 2 shows the timeline for the participants in the study. The *x*-axis is the time during the study in months. The participants will be randomized after baseline data is collected to an intervention group receiving whole-body vibration (WBV) in addition to PTH 1-34 compared to the control group receiving PTH 1-34 alone. After 12 months the intervention group will be re-randomized. *BMD* bone mineral density; *HR-pQCT* high-resolution peripheral quantitative computed tomography; *Bone biomarkers* procollagen type-1 amino-terminal propeptide (P1NP), carboxy-terminal type-1 collagen crosslinks (CTX), and sclerostin; *Physical markers*: Timed Up and Go (TUG), Short Physical Performance Battery (SPPB), grip strength and leg extensor power; *DXA* dual-energy x-ray absorptiometry; *IPAQ* The International Physical Activity Questionnaire; *FES-I* Falls Efficacy Scale International

After 12 months the combined PTH 1-34 + WBV group will be re-randomized to continuation of combined PTH 1-34 + WBV for another 12 months, or to PTH 1-34 alone (i.e., stopping WBV) for another 12 months. This will allow us to determine if any positive effects of WBV wear off after it has been stopped or if any gains persist.

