### Endpoints

#### Primary endpoints

The primary endpoint is the percent change in areal BMD of total hip and lumbar spine as measured by dual-energy x-ray absorptiometry (DXA) (Hologic Discovery, Waltham, MA, USA) from baseline until 12 months (Table 2).

**Table 2 Tab2:** Primary and secondary endpoints

	Measurement	Site	Time (months)
Primary endpoints			
Δ Bone mineral density	DXA	Total hip Spinal region	12
Secondary endpoints			
Δ Bone mineral density	DXA	Total hip Spinal region	6, 18, and 24
Δ Bone microarchitecture	HR-pQCT	Distal radius Distal tibia	6, 12, 18, and 24
Δ Bone biomarkers	P1NP CTX, sclerostin	Serum	3, 6, 12, 18, and 24
Δ Physical biomarkers	TUG SPPB		3, 6, 12, 18, and 24
	Dynamometer	Hand grip	
	Nottingham power rig	Leg extensor	
Δ Quality of life	EQ-5D		12 and 24
Δ Fear of falling	FES-I		12 and 24
Physical activity	IPAQ		0, 12, and 24
Adherence to WBV	Training logbook		Continuously
Falls	Falls calendar		Continuously

*Δ* change from baseline; Time is measured in months; *DXA* dual-energy x-ray absorptiometry; *HR-pQCT* high-resolution peripheral quantitative computed tomography; *P1NP* procollagen type-1 amino-terminal propeptide; *CTX* carboxy-terminal type-1 collagen crosslinks; *TUG* Timed Up and Go; *SPPB* Short Physical Performance Battery; *FES-I* Falls Efficacy Scale International; *IPAQ* The International Physical Activity Questionnaire; *EQ-5D* EuroQoL 5-dimension, 5-level questionnaire, *WBV* whole-body vibration

BMD is chosen as an endpoint since it is an important determinant of fracture risk and is used to diagnose and assess response to treatment in osteoporotic patients [1, 21].

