#### Secondary endpoints

##### Bone mass

Change in areal BMD of total hip and lumbar spine is measured by DXA from baseline until 6, 18, and 24 months (Table 2).

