### Statistical analysis

#### Sample size determination

The inclusion of 32 participants (16 in each group) would give the study 80% power to detect a clinically significant additional increase of 22% in BMD with WBV (assuming a 9% increase of BMD in the PTH 1-34-alone group and 11% increase in the combined PTH 1-34 + WBV group, and assuming a standard deviation (SD) of the BMD increase of 2% [12]. Inclusion of 40 participants (20 in each group) will allow for a 20% dropout rate.

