#### Statistical methods and data managing

The intervention arm (PTH + WBV) is compared against the control arm for all primary analyses. We will use analysis of covariance (ANCOVA) and “percentage change” for primary outcome adjusting for baseline measurements. For secondary outcomes we will use a chi-squared test for binary outcomes, analysis of variance (ANOVA) and the *T* test for continuous outcomes, and for non-normally distributed continuous outcomes we will use log transformation or Wilcoxon’s match-pairs signed-rank test and the Kruskal-Wallis test.

All *p* values will be reported to four decimal places with *p* values < 0.001 reported as *p* < 0.001. STATA version 14 will be used to conduct analyses. For all tests, we will use two-sided *p* values with an alpha ≤ 0.05 level of significance.

The analyses will be conducted with the intention-to-treat method, and in order to investigate the effect of adherence and withdrawal a per-protocol analysis will be conducted. Missing data will be handled using multiple imputation. Study data is collected and managed using REDCap (Version 6.5.10 – © 2015 Vanderbilt University) electronic data capture tools hosted at the University of Southern Denmark [44]. Sequential study numbers will be allocated to study patients and entered into the recruitment log at the secure web database REDCap.

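### The month-12 re-randomisation is said to settle whether WBV gains wear off or persist, but about 8 to 10 women per group cannot reliably detect even complete loss of the assumed BMD effect

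*Protocol article*

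**What the plan says.** The Randomization section of the protocol article (text following the Fig. 2 legend) re-randomises only the combined PTH 1-34 + WBV group at 12 months, to continue or stop WBV for a further year. It states the purpose without qualification: "This will allow us to determine if any positive effects of WBV wear off after it has been stopped or if any gains persist".

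The section Sample size determination covers the first randomisation only: "The inclusion of 32 participants (16 in each group) would give the study 80% power". The planning values there are a gain of 9% with PTH 1-34 alone against 11% with WBV added, and an SD of 2% for that gain. Enrolment is raised to 20 per group for 20% dropout. No effect size, power, precision or persistence margin is given for the second randomisation.

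BMD at 18 and 24 months is a secondary endpoint. The Bone mass section measures it "from baseline until 6, 18, and 24 months", and the footnote to Table 2 defines the change symbol as "change from baseline; Time is measured in months". Under Statistical methods and data managing, baseline-adjusted ANCOVA is named for the primary outcome. Continuous secondary outcomes get ANOVA or a t test, and "we will use two-sided *p* values with an alpha ≤ 0.05 level of significance".

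**The concern.** The sentence on re-randomisation is a statement about what the design can deliver. The plan's own calculation needs 16 women per group for 80% power to see a 2-point difference with SD 2. The stop-versus-continue comparison has roughly half that number per group, because one arm is divided in two.

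The wording promises an answer in either direction. If the comparison has about even odds of missing complete loss, a non-significant result says little, and it should not be read as evidence that gains last.

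The endpoint adds to the difficulty. Change from the original baseline includes everything that happened in year one. That variation precedes the second randomisation, cannot be affected by it, and is left in by an unadjusted t test or ANOVA.

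**Working it through.** **Inputs from the article**
- Effect: 11% − 9% = 2 percentage points at 12 months (Sample size determination).
- SD of the BMD change: 2 points (same section). No second-year SD is given, so carrying 2 forward is an assumption.
- 20 enrolled per arm; 20 × 0.8 = 16 after dropout (same section).
- Two-sided alpha 0.05 (Statistical methods and data managing).
- The re-randomisation ratio is not stated; 1:1 is assumed. This gives 20/2 = 10 per group with no dropout and 16/2 = 8 per group with 20% dropout and no further loss in year two.

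**The plan's own figure**

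n per group = 2 × (1.96 + 0.842)² × SD²/δ² = 2 × 7.85 × 4/4 = 15.7, so 16. Normal-approximation power at 16 per group is 80.7% (exact noncentral t: 78.1%). 32/0.8 = 40. The plan's figures reproduce.

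**Stop versus continue with the same inputs**

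Standard error = SD × √(2/n). Power is from the noncentral t distribution with 2n − 2 degrees of freedom and noncentrality δ/SE. The 95% CI half-width is t(0.975; 2n − 2) × SE.

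| | 8 v 8 | 10 v 10 |
|---|---|---|
| SE | 2 × √(2/8) = 1.00 | 2 × √(2/10) = 0.894 |
| 95% CI half-width | 2.145 × 1.00 = 2.14 | 2.101 × 0.894 = 1.88 |
| Power, whole effect lost (2 points) | 46% | 56% |
| Power, half lost (1 point) | 15% | 18% |
| Power, gap of 3 points | 80% | 89% |
| Difference detectable with 80% power | 3.0 points | 2.6 points |

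The normal approximation gives 52% and 61% for the 2-point loss. With 8 versus 8, an observed difference of exactly zero would have an interval of ±2.14, which does not exclude loss of the full 2 points.

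**Sensitivity to the SD (2-point loss, 8 v 8 / 10 v 10)**
- SD 1.5: 70% / 80%.
- SD 2.5: 32% / about 40%.
- 80% power would need an SD of about 1.33 / 1.51.

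**Effect of using the month-12 value**

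If changes to month 12 and month 24 have within-woman correlation ρ, ANCOVA leaves a residual SD of 2 × √(1 − ρ²). The values of ρ are assumptions.

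| ρ | Residual SD | Power, 8 v 8 | Power, 10 v 10 |
|---|---|---|---|
| 0.5 | 1.73 | 58% | 69% |
| 0.7 | 1.43 | 74% | 84% |
| 0.8 | 1.20 | 87% | 94% |

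The degree of freedom spent on the covariate lowers these figures by less than one percentage point.

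**WBV-stop versus control**

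If the full 2 points persist after stopping, with SD 2:
- 8 v 16: SE = 2 × √(1/8 + 1/16) = 0.866, half-width 2.074 × 0.866 = 1.80, power 60%.
- 10 v 20: SE = 2 × √(1/10 + 1/20) = 0.775, half-width 2.048 × 0.775 = 1.59, power 70%.

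**The case against.** The strongest reply is that the month 18 and 24 endpoints are already labelled secondary, that no power is claimed for them, and that small secondary comparisons are ordinary. That stands as far as it goes. The point here is the unqualified claim, not the smallness of the comparison.

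The 2-point gap is also a choice. The article does not say that a second year of WBV adds nothing. If continuing added 1 point while stopping lost 2, the gap would be 3 points and power 80% to 89%. This stands as a condition on the result, but the article assumes no such gap.

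The calculation covers BMD only, while the quoted sentence speaks of any positive effects. Nothing is shown here about HR-pQCT, bone markers or function.

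The gain from the month-12 covariate is not guaranteed either. Suppose yearly changes were independent with SD 2 each (an assumption). Change from the original baseline would then have SD 2 × √2 = 2.83 and power of 26% to 32%, and the month-12 analysis would bring it only to 46% to 56%.

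Four stronger readings are tempting but not supported:
- *The comparison cannot detect loss at all.* Power of 46% to 56% means not reliably, rather than never.
- *Persistence could be inferred only from a null result.* The control group is followed to month 24, so a difference between WBV-stop and control would be positive evidence that some gain remains.
- *Stop and continue women will be pooled against control in year two.* No section says so. The intervention-versus-control comparison is specified for the primary analyses, and the primary endpoint is at month 12, before the split.
- *A null result would be reported as persistence.* That is a risk created by the wording, not something the article announces.

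**Conclusion.** The concern holds in limited form. The article's own planning inputs do not support the claim that the second randomisation will determine wear-off or persistence. For BMD, stop versus continue has about even odds (46% to 56%) of detecting complete loss of the assumed effect. Its confidence interval is about as wide on each side as that whole effect. A non-significant result would not show persistence.

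This rests on a 1:1 split, the planned 20% dropout with no further loss in year two, SD 2 carried forward, and a gap no larger than 2 points. A smaller SD, a strong correlation with the month-12 value or a wider gap would raise power. Second-year dropout, an unequal split or partial loss would lower it. The 12-month primary comparison is unaffected. The plan should be changed, because a stated purpose of the second year is overstated and the endpoint chosen for it is not the most informative one available.

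**What to change.** 1. Replace the claim with wording such as: stop versus continue is exploratory; the difference will be estimated with a 95% confidence interval, and persistence will not be inferred from a non-significant test.
2. For stop versus continue, analyse BMD at months 18 and 24 by ANCOVA or a mixed model with the month-12 value as covariate.
3. Report WBV-stop versus control with its confidence interval as the direct evidence on persistence. Adjust this contrast for the original baseline, not for month 12: the month-12 value is itself an outcome of the first randomisation, and adjusting for it would remove the gain in question. Its precision is also modest (half-width about 1.6 to 1.8 points).
4. Keep control, WBV-stop and WBV-continue as separate groups after month 12.

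The cost is wording in the protocol and analysis plan. The month-12 scan is already scheduled for the primary endpoint, so no extra participants, visits or scans are needed. The downside is a more modest stated claim.
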